### **Statistical analysis**

Participants' characteristics will be summarized using descriptive statistics (mean, standard deviation). The equivalence of groups at baseline in terms of demographic and clinical variables will be assessed using independent samples *t* tests for continuous variables and chi-square tests for categorical variables. Following an intention-to-treat principle, estimates of efficacy (Group and Time main effect, as well as Group x Time interactions) will be analyzed using a repeated-measure analysis of variance (ANOVA). The statistical significance level will be set at 5 % and missing data will be analyzed using multiple imputation methods.

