## Abstract

**Background:** Degenerative lumbar spinal stenosis is a prevalent condition in adults over the age of 65 and often leads to deconditioning. Although the benefits of surgery outweigh those of conservative approaches, physical rehabilitation may be used to improve function and to minimize the risk of persistent dysfunction. This study protocol was designed to establish the feasibility of a full-scale randomized controlled trial and to assess the efficacy of an active preoperative intervention program on the improvement of clinical parameters and functional physical capacity in patients undergoing surgery for lumbar spinal stenosis.

**Methods/Design:** Forty patients will be recruited and randomly allocated to one of the 2 treatment arms: 6 weeks supervised preoperative rehabilitation program (experimental group) or hospital standard preoperative management (control group). The intervention group will be trained three times per week, with each session aiming to improve strength, muscular endurance, spinal stabilization and cardiovascular fitness. Intensity and complexity of exercises will be gradually increased throughout the sessions, depending on each participant's individual progress. Primary outcomes are level of low back disability and level of pain. Secondary outcomes include the use of pain medication, quality of life, patient's global impression of change, lumbar extensor muscles endurance, maximum voluntary contraction of lumbar flexor and extensor muscles, maximum voluntary contraction of knee extensors, active lumbar ranges of motion, walking abilities, and cardiovascular capacity. Both the primary and secondary outcomes will be measured at baseline, at the end of the training program (6 weeks after baseline evaluation for control participants), and at 6 weeks, 3 and 6 months postoperatively.

**Discussion:** This study will inform the design of a future large-scale trial. Improvements of physical performances before undergoing lumbar surgery may limit functional limitations occurring after a surgical intervention. Results of this study will provide opportunity to efficiently improve spinal care and advance our knowledge of favorable preoperative strategies to optimize postoperative recovery.

**Trial registration:** US National Institutes of Health Clinical Trials registry NCT02258672, 10 February 2014.

**Keywords:** Prehabilitation, Exercise therapy, Lumbar spine, Spinal stenosis, Surgery

\* Correspondence: [contact]

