### Sample size

Determination of the sample size was guided by time constraints as well as by a thorough analysis of the patients' surgery rate conducted over a 1-year period at the recruitment site in accordance with our inclusion and exclusion criteria [20]. Furthermore, when one of the study goals is to obtain an estimate of variance in an outcome when an important difference between groups has already been identified (meaning that only the variance needs to be estimated), it is suggested that 10 to 20 participants per group is deemed sufficient to inform feasibility and to plan for a larger study [20].

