### Randomization

Treatment allocation will be made based on randomization and minimization methods. Minimization criteria have been decided based on factors identified by the neurosurgeons known to delay postoperative recovery and include presence of diabetes, objective motor deficits in the lower limbs (confirmed by electromyography), self-reported severe disability (ODI score  $\geq 41$  %) and smoking habit. Patients will be randomized following a computer-generated list of random numbers. An independent research assistant blinded to patient assignment will sequentially number the envelopes containing intervention assignments according to the computer-generated randomization. Opaque and sealed envelopes will be opened in front of the participants at the end of the initial assessment visit.

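### The model leaves out the four minimization factors, which can make the analysis conservative, and baseline 'equivalence' is assessed with significance tests that cannot show it at about 20 per arm

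*Protocol*

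**What the plan says.** **Allocation.** The Randomization section states: "Treatment allocation will be made based on randomization and minimization methods". The factors are diabetes, electromyography-confirmed motor deficit in the legs, an ODI score of at least 41% and smoking. On why they were chosen: "Minimization criteria have been decided based on factors identified by the neurosurgeons known to delay postoperative recovery". The same section also says: "Patients will be randomized following a computer-generated list of random numbers", with assignments placed in sequentially numbered envelopes.

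**Outcome model.** The Statistical analysis section specifies a repeated-measures ANOVA by intention to treat and lists its terms: "Group and Time main effect, as well as Group x Time interactions". No covariate is named. On the level: "The statistical significance level will be set at 5" per cent.

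**Baseline comparison.** The same section says "The equivalence of groups at baseline in terms of demographic and clinical variables will be assessed using independent samples" t tests, with chi-square tests for categorical variables. It gives no equivalence margin and does not say what follows from either result.

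**Size.** The Abstract states: "Forty patients will be recruited and randomly allocated to one of the 2 treatment arms". The Sample size section rests on site volume, time limits and a pilot rule that "10 to 20 participants per group is deemed sufficient to inform feasibility and to plan for a larger study". No effect size, SD or power is given.

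**The concern.** There are two linked problems.

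1. Balancing the arms on prognostic factors reduces the chance variation of the treatment contrast. A model that ignores those factors keeps their variance in the error term, so the reported standard error can exceed the true sampling variability. The test is then conservative and the confidence interval wider than it need be. This matters in a trial that is small and is meant to estimate treatment effects and variance for a larger one.

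2. A t or chi-square test looks for a difference. It cannot show equivalence, least of all with about 20 per arm. Under proper randomization any baseline difference is due to chance, so the test also answers no useful question. A reader of the results could take non-significance as reassurance about prognostic balance, or take one chance significant result as a failure of randomization.

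Both are choices the Protocol states. Neither is a detail it leaves open.

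**Working it through.** **Inputs from the Protocol.** N = 40 in two arms; 5% level; four minimization factors; model terms Group, Time, Group x Time. The ODI and pain questionnaires are collected at five time points: baseline, preoperative, 6 weeks, 3 months and 6 months.

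**Assumptions.** 1:1 allocation (40/2 = 20 per arm), two-sided tests, R2 of the four factors from 0 to 0.4, and prevalences of 20% diabetes, 30% motor deficit, 25% smoking and 50% ODI of at least 41%. Minimization uses a biased coin of 0.8. The Protocol gives none of these. Its N has no power basis, so there is no planned figure to reproduce; 20 per arm merely agrees with the upper end of its 10-to-20 rule.

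**Step 1: what the baseline tests can detect.** Noncentral t with 38 df and noncentrality d x sqrt(20/2) = 3.162d:

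| True imbalance d | Power |
|---|---|
| 0.3 SD | 15% |
| 0.5 SD | 34% |
| 0.8 SD | 69% |

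- An observed difference reaches p < 0.05 only at 2.024 x sqrt(2/20) = 0.64 SD.
- For a binary factor, 4/20 against 9/20 gives an uncorrected chi-square of 2.85 (p = 0.09). The first significant split from 4/20 is 10/20 (p = 0.047).
- In the other direction, the chance of at least one false alarm in k independent tests is 1 - 0.95^k: 40% for k = 10 and 64% for k = 20.

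**Step 2: omitting the factors, one between-group contrast.** With perfect balance, the ratio of unadjusted to adjusted SE is 1/sqrt(1 - R2). The other columns come from simulated minimization (N = 40, 3,000 trials per scenario, one value per patient, SE in SD units):

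| R2 | 1/sqrt(1 - R2) | Simulated SE, unadjusted v adjusted | Type I error, unadjusted | Power for 0.8 SD, adjusted |
|---|---|---|---|---|
| 0 | 1.00 | 0.315 v 0.320 | - | - |
| 0.1 | 1.05 | 0.315 v 0.304 | 3.8% | 72% |
| 0.2 | 1.12 | 0.315 v 0.286 | 3.0% | 78% |
| 0.3 | 1.20 | 0.316 v 0.269 | 2.9% | 81% |
| 0.4 | 1.29 | 0.317 v 0.247 | 2.0% | 88% |

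For R2 of 0.1 to 0.4, adjusted type I error is 4.5% to 4.8%, and unadjusted power is about 69% to 72% throughout. The simulated SE ratios are slightly below the closed form (0.315/0.304 = 1.04 up to 0.317/0.247 = 1.28) because balance is imperfect and adjustment uses 4 df.

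**Step 3: Group x Time.** Baseline is one of the time points, so the treatment effect shows mainly in this term. A factor effect that is constant over time cancels within each patient. What counts is therefore how much of the *change* the factors explain:

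- 0%: SE 0.314 unadjusted v 0.319 adjusted.
- 5%: 0.315 v 0.311.
- 20%: 0.315 v 0.285, with type I error 2.7% v 4.5%.

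With complete data, entering the factors as main effects only leaves the Group x Time standard errors unchanged. In an example with 40 patients and five time points they were 0.4167 with and without the covariates.

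**Step 4: if allocation is simple randomization.** The unadjusted test stays near its level (4.6% to 6.1% in simulation). Its SE is valid, and only less precise once the factors explain enough variance.

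**The case against.** The strongest reply has five parts.

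- **The main test is Group x Time.** The larger losses in Step 2 belong to a single between-group value, not to the planned interaction test. This stands. The loss carries over only if the factors predict change. Calling them factors that delay recovery suggests they do, but no figure is given.
- **Minimization may not have been carried out.** A pre-generated list in numbered envelopes does not fit allocation that depends on patient characteristics. This stands too, and makes the claim about standard errors conditional.
- **R2, the prevalences and the biased coin are assumed.** True; hence the range, which includes R2 = 0, where adjustment slightly enlarges the SE.
- **Covariates are often left to a statistical analysis plan.** This has limited force. The Protocol lists the model terms and prescribes the baseline tests, so there are stated choices to comment on. A plan that is not shown may still add covariates.
- **This is a pilot sized by feasibility, with no power target.** True, and it limits the consequence. But the trial is meant to estimate effects and variance, so precision still matters.

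A reader might infer two stronger things. One is that the planned standard errors are simply too large; the documents support this only under the conditions above. The other is that the trial will declare balance from non-significance. The word 'equivalence' invites that reading, but no such rule is written, and the Protocol also plans descriptive summaries of participants' characteristics.

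**Conclusion.** The point holds in two parts of different strength.

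The baseline tests are unsuitable whatever the prognostic value of the factors. With 20 per arm assumed, power is 34% for 0.5 SD and 15% for 0.3 SD, so they cannot support a statement of equivalence.

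Omitting the minimization factors is a conditional loss of precision. It requires that minimization is carried out and that the factors predict the analysed quantity, which for Group x Time means change. For a single between-group contrast at an assumed R2 of 0.1 to 0.4, the unadjusted 5% test runs at about 3.8% to 2.0%, and by the closed form its SE is 5% to 29% larger than the adjusted SE. Near R2 = 0 there is almost no gain or loss. The error is in the conservative direction: no bias and no inflation of false positives. Under simple randomization the unadjusted SE is valid but less precise. The consequence is moderate, and the remedy costs little.

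**What to change.** 1. **Model.** Analyse the post-baseline values with Group, Time, Group x Time, the baseline value of the outcome as a continuous covariate, and the minimization factors. Use continuous baseline ODI in place of the 41% cut. Do not also keep the baseline value as a repeated outcome, or it sits on both sides of the model. Read the treatment effect from the Group contrasts, overall and by visit, where the covariates can reduce the error.
2. **If baseline stays as a repeated time point,** add factor x Time terms, because main effects alone do not change Group x Time.
3. **Baseline data.** Delete the t and chi-square tests and the word 'equivalence'. Show characteristics by arm as mean and SD, or number and per cent.

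**Cost.** The data are already needed for allocation. For ODI, the three binary factors plus continuous ODI take 4 df (38 to 34; critical t 2.024 to 2.032). For pain, its own baseline value adds one more (33 df; 2.035). The alternative in item 2 costs more: with five time points, four factors by four time contrasts take 16 of the 38 x 4 = 152 within-patient df. If the factors turn out not to be prognostic, the SE rises slightly (0.315 to 0.320).

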### Data collection

This study will take into consideration the evaluation of both clinical parameters (pain intensity, lumbar disability, use of pain medication, quality of life) and physical functional capacities (endurance and strength of lumbar region muscles, lumbar ranges of motion, walking abilities, cardiovascular capacity). All physical measures will be obtained during in-clinic assessments; at baseline, at the end of the training program (6 weeks after baseline evaluation for control participants), and at 6 weeks postoperatively and will provide insight into why the prehabilitation program was successful or not. In addition, self-reported questionnaires will be mailed at 3 and 6 months postoperatively in order to provide a subjective evaluation of patients' recovery at mid-term and long-term. The timeline illustrating the various interventions and outcome assessments is presented in Table 1.

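### The efficacy sentence lists the Time main effect, which compares no treatments, and a Group main effect diluted if baseline is a Time level, and names no single treatment difference

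*Protocol*

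**What the plan says.** The Statistical analysis section fixes the model and states what counts as efficacy: "estimates of efficacy (Group and Time main effect, as well as Group x Time interactions) will be analyzed using a repeated-measure analysis of variance". It adds "The statistical significance level will be set at 5" per cent and "missing data will be analyzed using multiple imputation methods". It does not say which of the three effects is the treatment effect, at which visit it applies, or whether baseline enters as a repeated measurement or as a covariate.

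The visits come from elsewhere in the protocol. The Abstract says "Both the primary and secondary outcomes will be measured at baseline, at the end of the training program", "and at 6 weeks, 3 and 6 months postoperatively", which makes five visits for the primary outcomes. For the physical measures, the Data collection section says "All physical measures will be obtained during in-clinic assessments; at baseline, at the end of the training program", followed by 6 weeks after surgery. That makes three visits, as in Table 1, although the Abstract implies five for every outcome.

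Three further points matter here:
- Under Recruitment, allocation is revealed after the baseline assessment.
- Under Eligibility criteria, every participant is awaiting surgery. Table 1 places the operation between the second and third assessments.
- The last paragraph of the Background gives the estimation aim as the effect of treatment on postoperative status.

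**The concern.** A main effect of Time averages over the two arms, so it contrasts visits and not treatments. With surgery between visits, it mostly reflects the operation and the natural course. Calling it an estimate of efficacy is wrong under any reading.

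A main effect of Group averages the arm difference over every level of Time. If baseline is one of those levels, the average includes a visit at which the expected difference is zero, and the estimate shrinks.

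Group x Time is a proper treatment comparison. Its F-test says whether the arms differ in their course, but not by how much or when.

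The Discussion presents the pilot as groundwork for a larger trial. A Time effect reported as efficacy could credit prehabilitation with the benefit of surgery. A diluted Group estimate, carried into a sample-size formula unchanged, would inflate the next trial by 1/0.8² = 1.6 to 1/0.6² = 2.8 times.

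**Working it through.** **Plan's own figure.** There is no power calculation to reproduce. The Abstract says "Forty patients will be recruited and randomly allocated to one of the 2 treatment arms", and the Sample size section relies on a rule of thumb: "it is suggested that 10 to 20 participants per group is deemed sufficient to inform feasibility and to plan for a larger study". Assuming 1:1 allocation, 40/2 = 20 per arm, the top of that range.

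**Assumptions.** The protocol gives no effect size, SD or correlation. I take an SD of 1 at each visit, equal correlation ρ between visits (0.5, range 0.3 to 0.7), a true effect d = 0.7 SD, two-sided 5% and complete data.

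**Step 1: Time with no treatment effect.** Let both arms shift by 1 SD at the three postoperative visits. The squared deviations of (0, 0, 1, 1, 1) from their mean sum to 3 − 9/5 = 1.2. The noncentrality is 40 × 1.2/(1 − 0.5) = 96 on 4 and 152 df, so power is essentially 100%. A simulation of 4,000 trials gave rejection rates of 100% for Time, 4.9% for Group and 5.3% for Group x Time.

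**Step 2: dilution of Group if baseline is a Time level.** The expected Group effect is d × (visits with the effect)/(all visits).

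| Outcome | Effect present at | Fraction recovered |
|---|---|---|
| Primary, 5 visits | all 4 post-baseline visits | 4/5 |
| Primary, 5 visits | 3 postoperative visits | 3/5 |
| Physical, 3 visits | both post-baseline visits | 2/3 |
| Physical, 3 visits | 6-week visit only | 1/3 |

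As a check, simulating a true effect of 0.80 SD at all four post-baseline visits gave a mean Group estimate of 0.64 SD, which is 0.80 × 4/5.

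**Step 3: power, effect at the three postoperative visits, ρ = 0.5.**
- Group: signal 0.6 × 0.7 = 0.42. Variance of the five-visit mean is (1 + 4ρ)/5 = 0.60. The noncentrality is 0.42/√0.60 × √(20/2) = 1.71 on 38 df, giving power 39%.
- Group x Time: noncentrality is (20/2) × 0.7² × 1.2/(1 − ρ) = 11.76 on 4 and 152 df, giving power 78%.
- Baseline-adjusted mean of the three visits: signal 0.70. Variance is (1 + 2ρ)/3 − ρ² = 0.667 − 0.25 = 0.417. The noncentrality is 0.70/√0.417 × √10 = 3.43, giving power 92%.

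The same formulas over the range of ρ give:

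| ρ | Group | Group x Time | Baseline-adjusted mean |
|---|---|---|---|
| 0.3 | 50% | 61% | 90% |
| 0.5 | 39% | 78% | 92% |
| 0.7 | 32% | 95% | 97% |

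If the 0.7 SD effect is present at all four post-baseline visits and ρ = 0.5, the figures are 61%, 58% and 94%, with the adjusted mean taken over those four visits.

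**Step 4: source of the advantage over Group at ρ = 0.5.** The squared signal-to-noise ratio is (1/0.6)² × (0.60/0.417) = 2.78 × 1.44 = 4.0. Most of it is removal of dilution. The variance ratio alone is 1.44 (0.44/0.443 = 0.99 at ρ = 0.3; 0.76/0.31 = 2.45 at ρ = 0.7).

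**The case against.** The strongest reply is that the same sentence also names Group x Time. That term compares the arms' course over time, is not diluted by baseline, and is not confounded by an operation that both arms undergo. A reader might infer that the planned efficacy analysis as a whole is biased toward zero or meaningless. The document does not support that: Group x Time is valid, and the Group test keeps its 5% level, so only the size of its estimate suffers.

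Other parts of the reply also stand:
- The dilution is an inference. The section does not say that baseline is a level of Time. It is the natural reading of a repeated-measures ANOVA over the listed visits with no covariate, but no more than that.
- Sphericity correction, covariance structure and follow-up contrasts commonly belong in an analysis plan, which is not shown. Their absence is not part of this point. Multiple imputation is a valid stated choice.
- The power comparison flatters the adjusted mean, because it averages exactly the visits where the effect was placed, at equal size. At ρ = 0.7 its lead over Group x Time is only about 2 percentage points.
- This is a pilot sized for feasibility and variance estimation. Arm-by-visit means and SDs are available whichever F-test is run, so it would be wrong to infer that the next trial could not be planned.

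The reply does not rescue Time as an efficacy estimate. Nor does it supply the single postoperative difference that the Background promises.

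**Conclusion.** The point holds in limited form. Of the three effects called efficacy estimates, Time is not a treatment comparison, and this does not depend on any assumption about baseline. Group is reduced to 4/5 or 3/5 of the true effect for the primary outcomes, and to 2/3 or 1/3 for the physical measures, provided that baseline is a Time level. Group x Time is sound as a test, but for the primary outcomes it is an omnibus test with 4 df, and no effect or contrast is named as the treatment difference.

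The power figures depend on the assumed 0.7 SD effect, equal correlation and 20 per arm. The dilution fractions do not depend on those values; they need only a zero expected baseline difference and an equal effect at the visits named. This should be corrected, but it does not invalidate the trial.

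**What to change.** In the Statistical analysis section, remove the Time main effect and the all-visit Group main effect from the efficacy estimates, and present Time descriptively. State as the efficacy estimate the between-group difference with 95% CI, adjusted for the baseline value of the outcome:

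- (a) at the preoperative visit; and
- (b) averaged over the three postoperative visits, or at the single 6-week postoperative visit for the physical measures.

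ANCOVA, or a mixed model on the post-baseline visits, would serve equally well. The stated multiple imputation can stay. Group x Time may be kept as a supporting test. The Abstract should also be aligned with Data collection and Table 1 on the visits at which physical measures are taken.

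The cost is a few sentences. Baseline is already collected, so no new data, visits or participants are needed.

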### Recruitment

Participants will be recruited at the *Centre de Santé et de Services Sociaux de Trois-Rivières* during their encounter with their treating neurosurgeon once the decision has been made to move forward with a surgical intervention. If deemed eligible, patients willing to participate in the study will be provided with an overview of the study purpose and content and they will be asked permission to be contacted by the research team. Further details will be given over the phone by a member of the research team and an assessment date will be set for the participant. Participants will be guided through the informed consent process and baseline demographics and physical measures will be collected. At the end of the initial assessment visit, a member of the research team will open the sealed envelope to randomly allocate participants to one of the two groups (intervention versus control). Treatments will be schedule after randomization for participants in the intervention group.

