### Measures of feasibility

Full-scale trial feasibility will be assessed by recruitment rate (and reasons for non-participation) and attrition rate, adherence to the protocol and safety of the intervention. Adherence to the prehabilitation protocol will be monitored through the kinesiologist's logbook. For every participant, date of encounter and exercises

[figure not shown]

**Fig. 1** Progression of squat exercise

**Table 1** Schedule of interventions and outcome measures

| Time point                                 | Location          | Data collection                                      |
|--------------------------------------------|-------------------|------------------------------------------------------|
| Baseline assessment                        | In clinic (UQTR)  | Questionnaires a
Physical measurements |
| 6 weeks prehabilitation                    | In clinic (UQTR)  | Physical fitness evolution                           |
| Post-intervention, Preoperative assessment | In clinic (UQTR)  | Questionnaires
Physical measurements              |
| Surgery                                    | Hospital (CSSSTR) | Perioperative data b                      |
| 6-week follow-up                           | In clinic (UQTR)  | Questionnaires
Physical measurements              |
| 3-month follow-up                          | Mailing           | Questionnaires c                          |
| 6-month follow-up                          | Mailing           | Questionnaires c                          |

aQuestionnaires include NRS, ODI, EQ-5D-3 L, Tampa Scale of Kinesiophobia, and BDI

bPerioperative data refers to blood loss, length of surgery and intraoperative complications

cIn addition to the regular questionnaire packet, a home-made questionnaire regarding physical activities undertaken during the postoperative phase will be mailed to the participants

BDI Beck Disability Index, CSSSTR Centre de Santé et de Services Sociaux de Trois-Rivières, EQ-5D-3 L EuroQol-5D-3 L, ODI Oswestry Disability Index, NRS Numerical Rating Scale, UQTR Université du Québec à Trois-Rivières

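### The Group main effect named as an efficacy estimate averages in the pre-allocation baseline visit on the ordinary reading, so it understates a constant effect by one fifth; baseline belongs in the model as a covariate

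*Protocol*

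**What the plan says.** The Statistical analysis section of the protocol gives the efficacy analysis in one sentence. Its targets are "estimates of efficacy (Group and Time main effect, as well as Group x Time interactions", and these "will be analyzed using a repeated-measure analysis of variance (ANOVA". It mentions no covariate. The only other stated use of baseline is a comparison of the groups by t test or chi-square test.

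The visits come from other sections. The Abstract says: "Both the primary and secondary outcomes will be measured at baseline, at the end of the training program", "and at 6 weeks, 3 and 6 months postoperatively". That makes five occasions, with baseline first. Table 1 places a questionnaire packet at all five, and its footnote reads "Questionnaires include NRS, ODI, EQ-5D-3 L, Tampa Scale of Kinesiophobia, and BDI", so both primary outcomes (ODI and pain NRS) are collected five times. Physical measures have three occasions under Data collection and Table 1: "All physical measures will be obtained during in-clinic assessments; at baseline, at the end of the training program", and then 6 weeks after surgery.

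Allocation comes after the baseline measures. Recruitment states: "At the end of the initial assessment visit, a member of the research team will open the sealed envelope". Randomization says the same: "Opaque and sealed envelopes will be opened in front of the participants at the end of the initial assessment visit".

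**The concern.** Nobody has been allocated when the baseline values are recorded, so the true group difference at that visit is zero. A Group main effect is the between-group difference averaged over the levels of Time. If baseline is one of those levels, a known zero enters the average and pulls a real effect towards zero. Any chance difference at baseline enters the same average directly, and also through its correlation with the later visits.

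The Background gives estimation of treatment effects as a purpose of the pilot, and the Discussion presents the results as preparation for a larger trial. If the diluted figure were used to plan that trial, the required sample size, which varies as 1/effect², would be inflated by 1/0.8² = 1.56 for the same SD. The baseline values that would sharpen the estimate are already being collected.

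**Working it through.** **Inputs from the protocol.** There are 40 patients; an equal split gives 40/2 = 20 per arm, the upper end of the 10 to 20 per group in the Sample size section. There are five visits for ODI and NRS and three for physical measures. The significance level is 5%. The protocol gives no effect size, SD, correlation or power, so it has no figure of its own to reproduce.

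**Assumptions.** Equal arms, complete data, two-sided test, SD 1 at every visit, the same correlation rho between any two visits (0.3, 0.5, 0.7), and an effect d = 0.7 SD at all post-baseline visits.

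**Dilution.** For five visits, (0 + 4d)/5 = 0.8d; with d = 0.7 this is 0.56. For three visits, (0 + 2d)/3 = 0.67d. These factors do not depend on SD, rho or sample size.

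**Chance imbalance.** Under simple randomization the standard error of the baseline difference is √(2/20) = 0.32 SD. A baseline difference of that size shifts the Group main effect by 0.316 × (1/5 + 4rho/5) = 0.14, 0.19 and 0.24 SD at rho 0.3, 0.5 and 0.7.

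**Standard errors.** SE = √(2v/20), where v is the variance per patient:
- Group main effect over five visits: v = (1 + 4rho)/5. At rho 0.5, v = 0.60 and SE = 0.245.
- Mean of four post-baseline visits, adjusted for baseline: v = (1 + 3rho)/4 − rho². At rho 0.5, v = 0.375 and SE = 0.194.
- One post-baseline visit, adjusted for baseline: v = 1 − rho². At rho 0.5, v = 0.75 and SE = 0.274.

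**Group x Time over five visits.** The F test has 4 and 4 × 38 = 152 df. Its noncentrality is (20/2) × Σ(e − ē)²/(1 − rho), where e is the group difference at each visit. For a constant d, Σ(e − ē)² = 0.8d² = 0.392, which gives 5.60, 7.84 and 13.07.

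**Power for a constant 0.7 SD effect** (noncentral t with 38 df for the Group main effect and 37 df for the adjusted analyses; noncentral F for Group x Time):

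| Analysis | Expected value | rho 0.3 | rho 0.5 | rho 0.7 |
|---|---|---|---|---|
| Group main effect, five visits | 0.56 | 74% | 61% | 51% |
| Group x Time, 4 df | no single value | 43% | 58% | 83% |
| Adjusted mean, four visits | 0.70 | 94% | 94% | 98% |
| Adjusted difference, one visit | 0.70 | 62% | 70% | 86% |

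For power equal to the adjusted mean, the Group main effect needs (v of Group main effect/0.64)/(v of adjusted mean) = 1.8, 2.5 and 4.2 times the patients.

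**A different effect shape.** Take an illustrative fading effect of 0.70, 0.35, 0.20 and 0 SD at the four post-baseline visits. Its mean is 1.25/4 = 0.3125. At rho 0.3, 0.5 and 0.7, Group x Time over five visits has 37%, 51% and 76% power; the adjusted mean has 34%, 35% and 44%.

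**The case against.** The strongest reply is that the plan already contains an undiluted term. Group x Time tests whether change differs between groups, and in a pre/post repeated-measures ANOVA it is usually read as the treatment effect. This stands. A reader might infer that the pilot's effect size is bound to be biased towards zero. The protocol does not support that, because it never says which of the three terms will be carried forward. Against Group x Time there remain three points: it is a 4-df test for the five-visit outcomes, it yields no single effect estimate, and it does not use baseline as a predictor.

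Second, the protocol does not say in words that baseline is a level of Time, and a statistical analysis plan could settle this. That is true, so the reading is inferred from the listed visits and the absence of a covariate. But it is the protocol itself that calls the Group main effect an efficacy estimate.

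Third, minimization uses ODI ≥ 41%, which limits imbalance in one primary outcome, so 0.32 SD probably overstates it for ODI. A dichotomised score does not remove the imbalance, and pain NRS is not a minimization factor. Imbalance is also random error and not bias on average.

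Fourth, one might infer that adjustment brings power of 94% or more wherever it is applied. It does not. That figure belongs to the mean of four visits under a constant effect. At rho 0.3 a single-visit adjusted difference (62%) has less power than the diluted Group main effect (74%). Surgery falls between the second visit and the last three, so a constant effect is not the obvious default, and with a fading effect Group x Time does better than the adjusted mean.

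Finally, the sample was set by time constraints and a pilot rule and not by a power target. The percentages therefore compare analyses; they do not measure failure against a stated goal.

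**Conclusion.** The point holds in a limited form. On the ordinary reading, one of the named efficacy estimates is 0.8 of a constant effect for ODI and NRS, and two thirds for the physical measures. It also carries baseline imbalance as noise. These two factors need only the visit schedule and a constant effect. The understatement reaches the larger trial only if the Group main effect is the figure used to plan it. The Time main effect cannot fill that role, because it does not compare the groups.

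The gain in precision from adjustment (SE 0.194 against 0.245 at rho 0.5) rests on 20 per arm, equal correlations, complete data and averaging over the four later visits. The advantage over Group x Time rests further on the effect not fading. A change is worth making because it is nearly free, but the protocol does not show that the planned analysis as a whole is invalid.

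**What to change.** In the Statistical analysis section:

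- Use the post-baseline values of each outcome as the responses, with the baseline value of the same outcome as a covariate.
- Keep Group x Time over the post-baseline visits, so that a changing effect can be seen. With four visits it has 3 df and tests only whether the adjusted difference varies between visits.
- Report the adjusted group difference averaged over the post-baseline visits, and at each visit, with 95% confidence intervals.
- Drop the all-visit Group main effect as an efficacy estimate.

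The cost is one sentence of text and one degree of freedom for the covariate. No new data are needed. The per-visit differences are less precise than the average and there are four per questionnaire outcome, so they are best read as estimates and not as four separate tests.
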